## Abstract

**Aims:**

Acute decompensated heart failure (ADHF) is often treated with diuretic agents in both the inpatient and ambulatory settings, yet fluid overload frequently persists and is associated with rehospitalization and death. In patients with predominant interstitial fluid expansion but without intravascular overload, increasing the loop diuretic dose or adding a second diuretic may cause intravascular volume depletion, electrolyte disturbance, and worsening renal function without clearing the excess tissue fluid. COMPRESSION-HF tests whether adding lower limb compression to standard diuretic treatment improves early decongestion in patients with ADHF, predominant peripheral oedema, and inferior vena cava (IVC) diameter ≤21 mm.

**Methods:**

COMPRESSION-HF (NCT06418932) is an investigator-initiated, multicentre, randomized, double-blind, sham-controlled trial in which adults with ADHF, bilateral leg oedema (grade II or higher of IV), N-terminal pro–B-type natriuretic peptide (NT-proBNP >1000 pg/ml), and IVC diameter ≤21 mm were assigned 1:1 to active bilateral lower limb compression (two-layer inelastic–elastic bandaging; manufacturer-specified nominal ankle pressure, approximately 20 mm Hg) plus parenteral furosemide or to sham bandaging plus parenteral furosemide, for up to 72 h. The two co-primary endpoints are 24-h urinary sodium excretion and change in body weight from baseline. Secondary endpoints include changes in lower limb circumference, clinical congestion score, and IVC diameter, together with NT-proBNP at 72 h, cumulative 72-h furosemide-equivalent dose, carbohydrate antigen 125 (CA-125) at day 15 ± 3, and 30-day safety. Continuous endpoints will be analysed with mixed-effects analysis of covariance or repeated-measures models including centre as a random intercept. Recruitment is complete (106 patients randomized); the trial was powered to detect a 20 mmol between-group difference in 24-h urinary sodium excretion.

**Conclusions:**

COMPRESSION-HF will show whether adding lower limb compression to standard loop diuretic treatment increases natriuresis and weight loss in patients with ADHF and predominant peripheral oedema, and will describe the relationship between tissue congestion, intravascular refilling, and the diuretic response.

## Introduction

Congestion is the main reason why patients with acute decompensated heart failure (ADHF) seek urgent medical care, and persistent congestion is strongly associated with death and readmission.^1–3^ However, congestion is not a uniform state. Excess extracellular fluid is distributed between two compartments that remain in dynamic equilibrium: the intravascular compartment, represented by plasma volume and venous pressures, and the extravascular compartment, represented by interstitial and third-space fluid. Although many patients have both intravascular and tissue congestion, the relative contribution of each compartment varies and influences the response to decongestive treatment.^4,5^

Loop diuretics promote renal sodium and water excretion and initially reduce plasma volume. When the response is sustained, vascular filling pressures fall, Starling forces at the microcirculation are modified, and interstitial fluid is expected to return to the vascular compartment for subsequent renal elimination.^6^ Decongestion can therefore be understood as a sequential process in which the intravascular compartment is depleted first and the interstitial compartment second. In clinical practice, this sequence is often incomplete. Plasma refill decreases during decongestion, and the interstitium is not a passive reservoir of free water. Its glycosaminoglycan-rich matrix binds sodium and water and, when oedema is established, becomes more compliant, favouring persistent tissue fluid accumulation.^7,8^

In patients with predominant tissue congestion and a relatively non-congested intravascular compartment, further increases in loop diuretic dose or the addition of a second diuretic may produce intravascular volume depletion, electrolyte disturbances, and worsening renal function without achieving proportional tissue decongestion.^9^ Pharmacological strategies intended to improve fluid transfer or restore effective circulating volume, including hypertonic saline, albumin, and osmotic approaches, have yielded inconsistent results and lack robust randomized support.^10–15^ Direct strategies to facilitate interstitial fluid mobilization therefore remain an unmet clinical need.^6,7^

Lower limb compression offers a simple, non-pharmacological strategy to facilitate tissue decongestion. By increasing interstitial hydrostatic pressure and venous return, compression may promote movement of interstitial fluid into the vascular and lymphatic compartments, increasing the substrate available for renal excretion during loop diuretic therapy.^16^ This rationale was tested in a single-centre pilot study of 20 patients with ADHF. The median baseline inferior vena cava (IVC) diameter was 14.5 mm [interquartile range (IQR), 14–20] in patients with an IVC ≤21 mm and 27.0 mm (IQR, 25–28) in those with an IVC >21 mm. Following compression, IVC diameter increased by 2.4 mm [95% confidence interval (CI), 1.0–3.8; *P* < .001] in the lower-IVC subgroup and by 0.8 mm (95% CI, −0.6 to 2.2; *P* = .611) in the higher-IVC subgroup (*P* for interaction <.001). This pattern suggested greater capacity for intravascular refill in patients without marked baseline central venous distension, and the refill response was accompanied by greater natriuresis and clinical decongestion.^17^

These findings generated the hypothesis of COMPRESSION-HF. The trial was designed to test whether adding lower limb compression to standard parenteral loop diuretic therapy improves early decongestion in patients with decompensated heart failure, predominant tissue congestion, and no marked intravascular congestion, defined by bilateral tibio-malleolar oedema and IVC diameter ≤21 mm. Here, we present the rationale and design of the trial.

## Methods

### Study design and oversight

COMPRESSION-HF is an investigator-initiated, multicentre, randomized, double-blind, sham-controlled trial to assess whether adding bilateral lower limb compression plus parenteral diuretic therapy, compared with sham compression plus parenteral diuretic therapy, improves early decongestion in patients with ADHF and predominant tissue congestion (*Figure 1*). Patients are randomized 1:1, and the intervention is applied for a minimum of 24 h and a maximum of 72 h, with follow-up to 30 days. Structured assessments of clinical congestion, body weight, lower limb circumference, urinary sodium excretion, diuretic exposure, renal function, NT-proBNP, carbohydrate antigen 125 (CA-125), IVC diameter, clinical congestion score, and safety are performed at scheduled visits.

**Figure 1 xvag214-F1:**
[figure not shown]
Overall study design and schedule of assessments from screening to 30-day follow-up

Ethical approval was obtained from the relevant ethics committee and the Spanish competent authority. The study is conducted in adherence to the principles of the Declaration of Helsinki, Good Clinical Practice guidelines, Regulation (EU) 2017/745 on medical devices, and applicable Spanish regulatory requirements. Written informed consent is obtained from all participants before any study-specific procedure. The trial is registered at ClinicalTrials.gov (NCT06418932). Enrolment commenced on 27 May 2024 and was concluded on 21 April 2026, with 106 patients randomized.

### Study population

Eligible patients are adults with ADHF requiring parenteral loop diuretic therapy and a congestion phenotype characterized by bilateral lower limb oedema without marked intravascular congestion. Patients can be enrolled from inpatient or ambulatory settings when all eligibility criteria are fulfilled.

The key selection criterion is the coexistence of clinically relevant peripheral tissue congestion and an IVC diameter ≤21 mm. This threshold was chosen to enrich the trial for patients in whom tissue-to-vascular fluid recruitment, rather than additional vascular unloading alone, is the expected limiting step for decongestion. Screening also requires NT-proBNP >1000 pg/ml and excludes conditions in which compression is unsafe or that may confound interpretation of decongestion (*Table 1*).

**Table 1 xvag214-T1:** Key eligibility criteria

Inclusion criteria	Exclusion criteria
Age ≥18 years	Admission to an intensive care unit
Clinical diagnosis of acute decompensated heart failure within 96 h after initiation of parenteral diuretic therapy	Renal transplant, chronic kidney disease Stage 5, estimated glomerular filtration rate <15 ml/min/1.73 m^2^, dialysis, or need for ultrafiltration
Treatment with furosemide ≥40 mg within the preceding 24 h	Absent peripheral pulses
NT-proBNP >1000 pg/ml at any time since onset of decompensation	Ankle–brachial index <0.9
Bilateral tibio-malleolar oedema grade II or higher of IV at inclusion	History of severe peripheral arterial disease
Inferior vena cava diameter ≤21 mm on subcostal echocardiography at screening	Previous intolerance to compressive bandaging
	Heart failure secondary to acute myocardial infarction

NT-proBNP, N-terminal pro–B-type natriuretic peptide.

Eligibility requires a clinical diagnosis of ADHF within 96 h after initiation of parenteral diuretic therapy and treatment with at least 40 mg of furosemide during the preceding 24 h. The 96-h criterion therefore defines the maximum interval from treatment initiation to enrolment rather than a minimum duration of previous therapy.

### Randomization and blinding

After consent and confirmation of eligibility, patients are randomized 1:1 through an electronic platform (Pinvestiga) using permuted blocks. Patients, treating clinicians responsible for clinical decisions, outcome assessors, and investigators remain blinded to treatment allocation. Active and sham systems have a similar external appearance, and personnel responsible for bandage application are separated from subsequent clinical, echocardiographic, urinary, biomarker, and safety assessments.

### Standard care

All patients receive parenteral loop diuretic therapy and background heart failure care according to the treating physician’s judgement and contemporary guideline-based practice. Furosemide dose, route, timing, escalation, and transition to oral diuretics are not protocol-fixed. Diuretic exposure is prospectively recorded and converted to furosemide equivalents when required.

### Active compression intervention

Patients allocated to the active intervention receive bilateral lower limb compression with UrgoK2 Lite (Urgo Medical), a commercially available two-layer multicomponent bandage system designed to provide a manufacturer-specified nominal ankle pressure of approximately 20 mm Hg when applied according to the instructions for use. Interface pressure is not measured instrumentally in individual participants. The system includes a padded short-stretch inelastic layer and a cohesive long-stretch elastic layer. The short-stretch component provides stiffness during movement, whereas the cohesive outer layer maintains resting pressure and secures the bandage. Integrated PresSure System visual indicators guide the intended stretch and overlap during application (*Figure 2*).

### Sham compression

Patients allocated to the control group receive visually matched sham bandaging without therapeutic compression. The sham system consists of a non-compressive padded dressing covered by elastic tubular mesh, designed to reproduce the external appearance of active compression without delivering clinically relevant pressure. Sham bandaging is applied bilaterally and renewed on the same schedule as active compression.

Lower limb circumference is measured bilaterally at prespecified points 5 and 10 cm above the ankle at baseline, before initial bandage application, and at 24 and 72 h. At each follow-up assessment, the active or sham bandage is removed, and circumference is measured before application of the replacement bandage or final discontinuation of the intervention.

### Endpoints

The trial has two co-primary endpoints, both assessed at 24 h after randomization:

Change in body weight from baseline to 24 h.Total urinary sodium excretion during the first 24 h after randomization.

These endpoints provide complementary renal and clinical assessments of the early treatment response. Total 24-h urinary sodium excretion quantifies the natriuretic response. Body weight change was selected as a pragmatic, non-urine-based clinical measure that is routinely available in hospital and ambulatory practice and does not require complete timed urine collection.

Secondary endpoints include changes in lower limb circumference at 5 and 10 cm above the ankle at 24 and 72 h; changes in clinical congestion score at 24 and 72 h; changes in IVC diameter at 3, 24, and 72 h; change in NT-proBNP at 72 h; change in CA-125 at 15 ± 3 days; cumulative furosemide-equivalent dose during the first 72 h after randomization; and 30-day safety.

Safety endpoints include adverse events related to compression; symptomatic hypotension; electrolyte disturbances at 72 h (hyponatraemia <135 mmol/L, hypernatraemia >150 mmol/L, hypokalaemia <3.5 mmol/L, and hyperkalaemia >5.0 mmol/L); worsening renal function (doubling of serum creatinine, estimated glomerular filtration rate decline ≥50% from baseline, renal replacement therapy); worsening heart failure events; and all-cause mortality. Worsening heart failure events are defined as hospitalization for heart failure or an urgent heart failure visit requiring parenteral diuretic therapy in an unscheduled ambulatory clinic or emergency department visit without an overnight stay. Recurrent episodes are counted separately when separated by at least 14 days of clinical stability; events occurring during the same hospitalization or continuous episode of care are counted as one event.

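### The only named local-harm endpoint depends on a judgement that events were caused by compression, which the sham control makes unnecessary and which leaves the safety comparison open to distortion

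*Protocol article*

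**What the plan says.** The safety list in the Endpoints section begins "Safety endpoints include adverse events related to compression; symptomatic hypotension" and runs through electrolyte, renal and heart failure outcomes to "worsening heart failure events; and all-cause mortality". Apart from the first, the items are systemic, and none is defined by attribution to the bandage. Thirty-day safety is also a stated secondary endpoint.

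On the control arm, the Sham compression section says "Patients allocated to the control group receive visually matched sham bandaging without therapeutic compression", and "Sham bandaging is applied bilaterally and renewed on the same schedule as active compression". The Randomization and blinding section says "Patients, treating clinicians responsible for clinical decisions, outcome assessors, and investigators remain blinded to treatment allocation". It adds that "Active and sham systems have a similar external appearance" and that "personnel responsible for bandage application are separated from subsequent clinical, echocardiographic, urinary, biomarker, and safety assessments".

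For the circumference measurements at 24 and 72 h, the Sham compression section says "At each follow-up assessment, the active or sham bandage is removed, and circumference is measured before application of the replacement bandage" or before the intervention ends.

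**The concern.** Skin injury, blistering, pain or infection under a bandage reaches the named local-harm endpoint only after a causality judgement. Randomization and a sham control exist so that harm can be read from the difference between arms without asking anyone what caused each event. Filtering by relatedness gives up part of that protection.

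The judgement is also hard in this population. Mean age is 82.1 years, 96.2% have oedema at or above the knee and 43.4% have diabetes (Trial status and baseline phenotype; Table 2). A leg event therefore has a ready explanation other than the bandage. Depending on how the judgement is made, the reported harm could be too high or too low. Local tolerability is one of the things a reader will want to know about a simple mechanical adjunct.

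**Working it through.** **Inputs from the article.** 52 patients on active compression and 54 on sham (Trial status and baseline phenotype). The article gives no local event rate, no attribution probability and no calculation for this endpoint, so there is no planned figure to reproduce. All rates below are assumptions chosen to show the mechanism.

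**Step 1: where blinding is protected and where it is exposed.** Similarity is claimed for external appearance. Underneath, the active system is a short-stretch layer plus a cohesive elastic layer at a nominal ankle pressure of about 20 mm Hg. The sham is padding under tubular mesh with no clinically relevant pressure. Once the bandage is off, the external match no longer helps. The Discussion accepts that circumference may change through local displacement of fluid, so the bare leg may carry some information about allocation. Staff who apply bandages are kept apart from safety assessment, but the Sham compression section does not say who removes them or who inspects the skin.

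**Step 2: attribution that differs by arm.** Let the true risk of a leg event be p in both arms, so that compression adds nothing. Let a fraction 0.8 be attributed in the active arm and s in the sham arm. The spurious risk difference is p × (0.8 − s), in percentage points:

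| p | s = 0.8 | s = 0.6 | s = 0.4 | s = 0 |
|---|---|---|---|---|
| 5% | 0 | 1 | 2 | 4 |
| 10% | 0 | 2 | 4 | 8 |
| 20% | 0 | 4 | 8 | 16 |

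With p = 10% and s = 0.4, the expected counts are 52 × 0.10 × 0.8 = 4.2 active and 54 × 0.10 × 0.4 = 2.2 sham. The first column matters as much as the rest: with even attribution the spurious difference is zero at every p.

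**Step 3: even attribution, blinding intact.** Let the true risks be p₁ (active) and p₀ (sham). Let c be the fraction of compression-caused events that is attributed and b the fraction of background events that is attributed, the same in both arms.

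- Reported active risk = b × p₀ + c × (p₁ − p₀)
- Reported sham risk = b × p₀
- Reported excess = c × (p₁ − p₀)

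The absolute excess is therefore reduced by the proportion 1 − c, whatever b is. Take p₁ = 24%, p₀ = 12% and b = c = 0.4:

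- Active: 0.4 × 24% = 9.6%. Sham: 0.4 × 12% = 4.8%.
- Reported excess 4.8 points against a true 12 points, a fall of (12 − 4.8)/12 = 60%.
- Expected counts fall from 52 × 0.24 = 12.5 and 54 × 0.12 = 6.5 to 52 × 0.096 = 5.0 and 54 × 0.048 = 2.6.
- The risk ratio stays at 2, because b = c.

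**The case against.** A reader might infer that the comparison is biased as planned, because a sham patient has no compression and an event there can never truly be caused by it. The article does not support that. Sham patients do wear bilateral bandages, matched in appearance and renewed on the same schedule. Assessors are blinded, and those who apply bandages are kept out of safety assessment. A blinded assessor faces the same question in both arms, and a padded dressing can plausibly cause skin complaints too. Only someone who knows or guesses the arm would answer it differently. Step 2 shows that without such a difference no spurious excess arises. That the bare leg often reveals the arm is an assumption. This objection stands, and it limits the point to a risk.

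A reader might also infer that other leg events go unrecorded. The safety list is introduced as including its items, so it is not closed. Adverse-event collection, causality rules and full adverse-event tables are normally left to the full protocol or analysis plan. This stands too: nothing here says that data are missing.

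A third objection is that even under-attribution preserves the risk ratio, as in Step 3, and so is not bias between arms. That is correct for the ratio when caused and background events are attributed equally often. It does not rescue the absolute excess, which is what a clinician weighs, nor the number of events available. A relatedness filter costs nothing in Step 3 only if every caused event is recognised as such.

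**Conclusion.** The point holds as a weakness in a stated endpoint definition. The one local-harm item named rests on a causality judgement that the randomized sham comparison does not need.

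Uneven attribution is possible because the match between systems is external and the bandage comes off at 24 and 72 h, but it is not demonstrated. The loss of absolute excess under even attribution follows by algebra whenever fewer than all of the caused events are attributed.

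The size cannot be computed from the article. In the illustrations, the spurious excess runs from 0 to 16 points depending on how far attribution diverges, and a true 12-point excess falls to 4.8 points when 40% of events are attributed in both arms. These figures rest wholly on the assumed rates. The co-primary endpoints and the other listed safety outcomes are not affected.

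**What to change.** Before adverse events are examined by arm, define the local-harm endpoint as all lower-limb and skin adverse events from randomization to day 30. Use a prespecified list of terms, have the coding done by someone without access to allocation, and compare by randomized arm regardless of judged relatedness. Keep the relatedness judgement as a descriptive listing. Table 2 already shows baseline data by named arm, so the coding must be kept separate from anyone who holds the allocation.

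Use adverse events already recorded. Do not add findings noted only by bandage-application staff: they know which system was used, so this would bring unblinded ascertainment into the endpoint, and the article does not show that such records exist.

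The cost is a change of wording in the analysis plan and one additional table. Recruitment is complete, and no new data are needed. The downside is small: events due to background oedema will add some noise in both arms.

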### Statistical analysis

Continuous variables will be summarized as mean (SD) or median (IQR), according to distribution. Categorical variables will be summarized as counts and percentages. Baseline comparisons will use Student's *t*-test or the Mann–Whitney *U* test for continuous variables and χ^2^ or Fisher’s exact test for categorical variables.

All analyses will follow the intention-to-treat principle. The co-primary endpoints will be compared between groups at the prespecified 24-h time point using mixed-effects regression models with centre included as a random effect. Secondary endpoints assessed repeatedly after randomization will be analysed using mixed-effects models with random effects for centre and patient, and treatment effects will be estimated across the relevant post-randomization visits. All models will be adjusted for a prespecified set of baseline covariates selected *a priori* on the basis of their established prognostic association with the natriuretic and diuretic response, independently of their observed between-group balance: log-transformed baseline NT-proBNP, baseline estimated glomerular filtration rate, baseline parenteral loop diuretic dose, prior heart failure hospitalization, and the Charlson Comorbidity Index. For secondary endpoints with a repeated-measures structure, treatment comparisons will be adjusted for multiplicity using the Šidák method. Given the modest sample size, the trial is designed as a proof-of-concept study; the prespecified covariate-adjusted model will constitute the primary analysis, with unadjusted estimates reported for transparency. Statistical significance will be defined as a two-sided *P* < .05. All analyses will be performed in Stata 19 by an independent statistician (MedStats Consulting, Reading, PA, USA)

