**Figure 3 xvag214-F3:**
[figure not shown]
Participant flow. Of 108 patients who provided informed consent, 2 were screening failures (one ankle–brachial index <0.9; one inferior vena cava diameter >21 mm). A total of 106 patients were randomized: 54 to sham compression plus standard care and 52 to active compression plus standard care. All 106 patients were included in the 24-h body-weight analysis population; 99 patients had evaluable 24-h urinary sodium data

Among the 106 randomized participants, 30 (28.3%) were enrolled during hospitalization and 76 (71.7%) in the ambulatory setting. In ambulatory participants, parenteral furosemide was initiated as part of routine clinical care on the day of screening and randomization, before written informed consent and independently of study participation; consent was obtained before any study-specific procedure. Among hospitalized participants, the median duration of parenteral treatment before randomization was 48 h (IQR, 0–48). The median parenteral-equivalent furosemide dose before randomization was 120 mg/24 h (IQR, 80–160).

The enrolled population reflected the intended phenotype (*Table 2*). Mean age was 82.1 years, 57 patients (53.8%) were men, and mean left ventricular ejection fraction was 53.5%; only 17 patients (16.0%) had left ventricular ejection fraction <40%. Comorbidity burden was high, with chronic kidney disease in 53 patients (50.0%), diabetes in 46 (43.4%), and atrial fibrillation or flutter in 70 (66.0%). Peripheral oedema was extensive: 102 patients (96.2%) had oedema reaching at least the knee. In contrast, markers of intravascular and pulmonary congestion were modest, with a mean IVC diameter of 18.0 mm, and jugular venous distension in 20 patients (18.9%). Median NT-proBNP was 4132 pg/ml, and median CA-125 was 54.5 U/mL.

**Table 2 xvag214-T2:** Baseline characteristics of the randomized population

	Sham compression (*n* = 54)	Active compression (*n* = 52)	Total (*n* = 106)
Demographic and clinical characteristics			
Age, years	81.8 ± 9.4	82.4 ± 8.9	82.1 ± 9.1
Male sex	29 (53.7%)	28 (53.8%)	57 (53.8%)
Ambulatory enrolment	37 (68.5%)	39 (75.0%)	76 (71.7%)
Prior HF hospitalization	20 (37.0%)	27 (51.9%)	47 (44.3%)
Atrial fibrillation or flutter	35 (64.8%)	35 (67.3%)	70 (66.0%)
Chronic kidney disease	24 (44.4%)	29 (55.8%)	53 (50.0%)
Diabetes mellitus	19 (35.2%)	27 (51.9%)	46 (43.4%)
eGFR, ml/min/1.73 m^2^	48.0 (35.5–62.1)	39.0 (28.7–53.8)	41.4 (32.5–59.6)

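### The 72-h electrolyte safety count takes no account of baseline sodium or potassium, so abnormalities present at randomization add noise and carry any chance imbalance into the comparison

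*Protocol article*

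**What the plan says.** Protocol article, Endpoints: the safety endpoints include "electrolyte disturbances at 72 h (hyponatraemia <135 mmol/L, hypernatraemia >150 mmol/L, hypokalaemia <3.5 mmol/L, and hyperkalaemia >5.0 mmol/L". These are four absolute limits at one time point. The definition does not refer to the value at randomization. The renal item in the same sentence does, with "estimated glomerular filtration rate decline ≥50% from baseline".

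Protocol article, Statistical analysis: "All models will be adjusted for a prespecified set of baseline covariates", and the set is "log-transformed baseline NT-proBNP, baseline estimated glomerular filtration rate, baseline parenteral loop diuretic dose, prior heart failure hospitalization, and the Charlson Comorbidity Index". Baseline sodium and potassium are not in it.

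Protocol article, Study population, Table 1: there is no sodium or potassium criterion, and entry requires "Treatment with furosemide ≥40 mg within the preceding 24 h".

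Protocol article, Trial status and baseline phenotype: mean age is 82.1 years, and the cohort has "chronic kidney disease in 53 patients (50.0"%). Table 2 as shown gives no baseline sodium or potassium.

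**The concern.** Read as written, a patient with sodium of 132 mmol/L at randomization and 132 mmol/L at 72 h is a safety event in either arm. Nothing in the eligibility criteria keeps such patients out, and in an elderly, diuretic-treated cohort with much kidney disease some are likely.

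There are two consequences. First, patients who are abnormal throughout are events unrelated to treatment, so they blur the comparison. Second, if the arms differ by chance in baseline abnormality, the part that persists appears at 72 h as though it were a treatment difference. The planned covariates act on this only indirectly, through kidney function and diuretic dose. The article states no specific test for the safety items; if they are compared without a model, even that partial correction is absent.

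The endpoint matters to the trial's argument. The Abstract and Introduction name electrolyte disturbance as a harm of intensifying diuretics in this phenotype.

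**Working it through.** **The plan's own calculation.** The only one is for urinary sodium (Sample size), and it is not in dispute. A difference of 20 mmol with SD 30, two-sided 0.05 and 90% power gives 48 per arm, 96 in total. Then 96 × 1.10 = 105.6, so 106 (dividing by 0.90 gives 107). No calculation is given for the electrolyte endpoint.

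**Inputs.** From the article: 54 sham and 52 active patients. Assumed, because the article reports no electrolyte data: baseline prevalence *b*, persistence to 72 h *r*, and new-onset risk *p* among patients normal at baseline.

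**What the definition measures.** The 72-h proportion in an arm is *b·r* + (1 − *b*)·*p*. If *r* is the same in both arms, the risk difference is (1 − *b*) times the new-onset difference. With *b* = 20%, *r* = 70% and *p* = 8% v 25%:
- sham: 0.20 × 0.70 + 0.80 × 0.08 = 20.4%
- active: 0.20 × 0.70 + 0.80 × 0.25 = 34.0%
- difference 13.6 points instead of 17, and risk ratio 0.340/0.204 = 1.7 instead of 0.25/0.08 = 3.1

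**If persistence differs.** With the same *b* and *p* but *r* = 40% sham v 80% active:
- sham: 0.20 × 0.40 + 0.064 = 14.4%
- active: 0.20 × 0.80 + 0.20 = 36.0%
- difference 21.6 points, larger than the 17-point new-onset difference

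**Power.** Simulation of 54 v 52 patients, two-proportion z test at 1.96, *p* = 8% v 25%:

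| Baseline prevalence | Equal persistence 70%: 72-h count / new-onset count | Persistence 40% v 80%: 72-h count / new-onset count |
|---|---|---|
| 2% | 63% / 67% | not tabulated |
| 5% | 58% / 66% | not tabulated |
| 10% | 49% / 63% | 71% / 63% |
| 20% | 36% / 58% | 75% / 58% |
| 30% | 27% / 52% | 79% / 52% |

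A second set of assumptions (new onset 10% v 25%, equal persistence 80%, normal approximation) gives the same pattern as the equal-persistence column: 37% / 49%, 27% / 45% and 20% / 40% at *b* = 10%, 20% and 30%.

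**Keeping the 72-h count but accounting for baseline status.** At *b* = 20%, power rises from 36% to 44% with equal persistence, and from 75% to 81% with unequal persistence. The baseline-adjusted comparison beats the plain count in both scenarios across 5% to 30% baseline prevalence.

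**Chance imbalance.** The between-arm difference in baseline prevalence has SD √[*b*(1 − *b*)(1/54 + 1/52)]. At *b* = 20% this is √(0.16 × 0.03775) = 7.8 points, so a gap of 10 points or more, in either direction, arises in about 20% of randomizations. At *b* = 10% the SD is 5.8 points and the frequency about 9%. With no treatment effect and *p* = 8%, a 10-point gap gives 0.10 × (*r* − 0.08) at 72 h: 4.2 points at *r* = 50% and 6.2 points at *r* = 70%.

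**The case against.** **The article only lists the endpoint.** Treatment-emergent flags and shift tables are commonly left to the full protocol or SAP, and they may be there. That is fair for reporting detail. But the article itself sets the numerical limits and the time point, and fixes a covariate set for all models without baseline electrolytes. The point rests on that wording.

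**Kidney function and diuretic dose are already covariates.** This stands in part. Where a model is used, they remove some of any imbalance driven by kidney function. They do not stand in for the patient's own starting sodium or potassium.

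**The 72-h count is not inferior in general.** This stands. A reader might infer that the definition dilutes any signal of harm and should give way to a new-onset count. The documents do not support that. The dilution follows only if persistence is equal in the arms. Harm that prolongs an existing abnormality is caught by the 72-h count and missed by a new-onset count.

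**No electrolyte imbalance is shown.** This also stands. A reader might infer from the lower active-arm eGFR (median 39.0 v 48.0) and the greater share with chronic kidney disease (55.8% v 44.4%) that the active arm started with more abnormal electrolytes. That is plausible but undocumented. Moreover, in the 71.7% of patients enrolled as outpatients, parenteral furosemide began on the day of randomization, so it had little time to alter baseline values.

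**Low consequence.** The endpoint is an unpowered safety item in a proof-of-concept trial. That limits the weight of the point but does not remove it, because the correction is cheap.

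**Conclusion.** The point holds in limited form. As written, the endpoint is a 72-h prevalence, and the fixed covariates do not account for the starting value of the electrolyte concerned. The cost is precision and exposure to chance baseline imbalance. A reader might go further and call the comparison invalid. It is not: randomization makes any baseline difference a matter of chance, type I error stays at 5%, and no primary conclusion depends on it.

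The size turns on baseline prevalence, which is not reported: small at 2% to 5%, material at 10% to 30%. The direction relative to a new-onset count turns on persistence. If persistence is equal, the 72-h count understates new-onset harm; if compression alters it, the 72-h count can be the more sensitive. All power figures rest on assumed prevalence, persistence and new-onset risks, and on a single binary event where the article lists four. What does not depend on the persistence assumption, in the scenarios tested, is the gain from accounting for the baseline value. The change is worth making but not essential to the trial's validity.

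**What to change.** Keep the 72-h threshold count, and:

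1. Compare arms adjusted for, or stratified by, the baseline value of the same electrolyte.
2. Analyse 72-h sodium and potassium as continuous values, each adjusted for its own baseline.
3. Report new-onset and persistent abnormalities separately by arm, alongside the 72-h count and not in its place. Show baseline sodium and potassium by arm.

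Recruitment is complete, so this should be settled before comparative safety results are analysed. It needs no new patients or visits. The cost is SAP wording and slightly more analysis work. It assumes that baseline sodium and potassium were measured with the baseline eGFR sample, which the article does not state. If the full protocol or SAP already contains these steps, a cross-reference is enough.
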